### Eligibility criteria

Patients will have to fulfill all the following inclusion criteria:
Female or male patients, aged 18–70 yearsAn average spontaneous pain level of at least 4 on an 11-point numerical rating pain score (0 = no pain, 10 = worst pain possible) on at least 3 days during the week before the studyThe existence of tactile allodynia, as a sign of neuropathic pain, following a traumatic peripheral nerve injuryAbility to communicate in English or FrenchWilling and able to sign an informed consentStable pain disease with no anticipated change in treatment for the next 5 weeks.Female subjects of childbearing age must agree to use an effective method of contraception during the study period. Female subjects who utilize a hormonal contraceptive as one of their birth control methods must have consistently used the same method for at least 3 months before study drug dosing. Effective methods of contraception include double barrier methods [male condom (with spermicide), female condom (with spermicide), diaphragm with spermicide, cervical cap with spermicide or sponge with spermicide] or hormonal methods [oral contraceptives (either combined or progesterone only), injectable progesterone, subdermal contraceptive implant, transdermal contraceptive patch, contraceptive vaginal ring].

Any of the following conditions will exclude patients from this study:
Diabetes mellitus necessitating antihyperglycemic treatment or any other endocrine diseaseAny liver disease, resulting in liver transaminase enzyme levels greater than three times the normal valuesChronic renal failure or kidney disease, resulting in serum creatinine levels > 133 μmol/lHypertension or taking of anti-hypertensive medicationMalignant disease or taking of chemotherapeutic agentsKnown diagnosis of angina pectoris, arrhythmias, congestive heart failure, or peripheral arterial diseasePregnancy or breastfeeding. Female patients of childbearing age must have a negative urine pregnancy testKnown allergic reaction to clonidine or pentoxifyllinePresence of a medical condition known to affect peripheral circulation (intermittent claudication, peripheral arterial disease, Raynaud’s syndrome)Medication that interacts with clonidine or pentoxifylline [cardiovascular drugs such as angiotensin-converting enzyme inhibitors, alpha-blockers (prazosin, terazosin or doxazosin), beta-blockers (atenolol, metoprolol, propranolol), neuroleptics (butyrophenones, phenothiazines, thioxanthenes), calcium channel blockers (verapamil, diltiazem), and non-cardiovascular drugs such as diuretics, thyroxine, monoamine oxidase inhibitors, and selective serotonin reuptake inhibitors, as well as vitamin K antagonists and blood thinners like warfarin]Any medical condition that might be impacted by clonidine or pentoxifylline, such as cardiovascular disease, cardiac rhythm disorders (sinus node dysfunction, atrial-ventricular blockade, or other conduction abnormalities), orthostatic regulation disturbances, and disorders of cerebral perfusionA cerebral and/or retinal hemorrhage (in the last 5 years)

### Interventions

All participants will be randomized to treatment with either active drug or placebo in one of the two 2-week-long treatment blocks of the study. The active drug is an anhydrous topical solution containing 0.1% (W/V) clonidine and 5% (W/V) pentoxifylline. The placebo is a blank version of the anhydrous solution with constituents identical with the active drug except omitting the therapeutic agents, i.e., clonidine and pentoxifylline. The stability of the topical solutions at room temperature has been ascertained with mass spectrometric studies done upon the request of Health Canada. The exact composition of the active drug and placebo is as outlined in Table 2.

**Table 2 Tab2:** Composition of 100 ml of the active drug topical solution with 0.1% (W/V) clonidine and 5% (W/V) pentoxifylline

**Solid ingredients**		**Amount (g)**
1	Clonidine	0.1
2	Pentoxifylline	5.0
**Liquid ingredients**		**Amount (ml)**
3	Anhydrous ethanol	6.2
4	Polyethylene glycol 400	18.9
5	Oleyl alcohol	50.8
6	Propylene glycol	18.9

Both the active drug and placebo solutions are colorless and will be packaged in identical Topi-Pump® dose-metered applicators that dispense 1 ml of topical solution with each pump. Participants will be instructed to apply one pump or 1 ml of the topical solution three times daily on an eight-hourly basis. They will also be asked to return the emptied pumps after use so adherence to treatment can be monitored.

### Outcomes

Primary outcome measures of the study are as follows:
The average daily pain intensity level is recorded by the patient at home in an REB approved pain diary that contains a visual analog scale (VAS) displaying the words “no pain” and “worst pain possible” on the left and right of a 100-mm line, respectively.The degree of dynamic mechanical allodynia (DMA) is determined by stroking the most painfully sensitive area of the skin once at a velocity of 1–2 cm/s with a soft brush (bristle length by width: 20 × 15 mm). The patient then indicates the amount of pain evoked on an REB approved data collection sheet with a 100-mm VAS. This test will be stopped immediately at the request of the patient if it is too painful.

Secondary outcome measures of the study are as follows:
Pain relief scores are recorded on a 6-point categorical pain relief scale (0 worse pain to 5 complete pain relief).Area of punctate hyperalgesia (PHA) is measured using punctate stimulation with a 26-g von Frey monofilament (Semmes Weinstein Monofilament Kit; Stoelting, Wood Dale, IL). Stimulation commences from outside the sensitive area toward the center of the sensitive area, along eight approximately evenly spaced radii, while asking the subject to report when the sensation becomes unpleasant or frankly painful. The points at which the sensations change will be marked and the markings gently transferred onto a lightweight transparent plastic sheet. The marked sheet is subsequently photographed with a ruler to calibrate the number of pixels per unit length during image analysis and area calculation.

### Sample size

Thirty-two patients will be recruited for this trial. This number of patients is chosen based on the assumption that during the active topical drug treatment period patients will experience a reduction of either of the primary outcome measures (spontaneous pain or intensity of DMA) of 20 mm or more on the 100 mm VAS (standard deviation assumed: 25, i.e., Cohen’s *d* = 0.8, alpha = 0.025 corrected for multiple testing; power = 95%). Based on a power calculation for two groups using a cross-over design, the estimated required sample size is 27, and we expect that a sample size of 32 is sufficient to detect changes in pain levels even if up to 18% of patients do not complete the study.

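### The only multiplicity rule stated for the two primary outcomes is an equal split at 0.025 each; Holm's procedure would give more power on the second outcome at the same 5% family-wise error and no extra patients

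*Protocol article*

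**What the plan says.** The Outcomes section of the protocol article names two primary outcomes, both on a 100 mm VAS: daily spontaneous pain from the diary, and pain evoked by a brush stroke (DMA).

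The Sample size section counts an effect on one of them as enough: it assumes "a reduction of either of the primary outcome measures (spontaneous pain or intensity of DMA") "of 20 mm or more on the 100 mm VAS", with "standard deviation assumed: 25" and "alpha = 0.025 corrected for multiple testing; power = 95"%. It concludes: "Based on a power calculation for two groups using a cross-over design, the estimated required sample size is 27". Thirty-two patients are recruited to allow for dropout.

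The Statistical methods section says that unpaired t-tests between the two sequence groups will be used. It gives no significance level and no procedure for testing two primary outcomes. The level 0.025 appears nowhere else in the article.

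**The concern.** A level of 0.025 described as corrected, with two primary outcomes, is 0.05 divided by two. If each outcome is tested at that level regardless of the other, some of the 5% error budget is left unused. Once one null hypothesis has been rejected, only one remains, and it can be tested at the full 5% without raising the family-wise error.

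What is at stake is the second outcome. The Objectives section asks about both spontaneous and evoked pain, and the Discussion presents the two measures as covering both. Suppose one outcome succeeds and the other has a p-value between 0.025 and 0.05. A fixed split does not support a claim on that second outcome; Holm does.

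**Working it through.** **Inputs.** From Sample size: difference 20 mm, SD 25 mm (so d = 20/25 = 0.8), level 0.025 per outcome, power 95%, two primary outcomes, success on either. Sidedness is not stated. The correlation between the two outcomes is not given, so it is ranged over 0, 0.5 and 0.8. SD 25 is taken as the SD of within-patient differences, because only that reading gives the plan's 27. If 25 were the SD under each treatment with independent periods, the SD of differences would be 25√2, d would be 0.566 and the sample size 50.

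**Step 1: the plan's own figure.** For a t-test on within-patient differences, the noncentrality is d√n and the critical value is the 1 − 0.025/2 quantile of t with n − 1 degrees of freedom.
- n = 27: noncentrality 0.8 × √27 = 4.157, critical value 2.379, power 95.6%.
- n = 26: noncentrality 4.079, critical value 2.385, power 94.8%.

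So 27 is reproduced, also with n − 2 degrees of freedom. Two-sided 0.05 or one-sided 0.025 gives 23, and two-sided 0.0125 gives 31. Hence 0.025 is a two-sided level for each outcome, and the family-wise level is 0.025 + 0.025 = 0.05.

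**Step 2: error control under Holm.** The smaller p-value is tested at 0.025 and, if significant, the larger at 0.05.
- Both nulls true: a false claim needs the smaller p-value to be at most 0.025. Its probability is at most 0.025 + 0.025 = 0.05.
- One null true: a false claim needs that outcome's p-value to be at most 0.05. Its probability is at most 0.05.

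Neither bound uses the correlation. Simulation with n = 27 (200,000 trials per setting) gives 5.0%, 4.6% and 4.0% under the global null for correlations 0, 0.5 and 0.8, identical for the two procedures. With 20 mm on one outcome and none on the other, Holm's error on the null outcome is 4.8%, 4.7% and 4.5%.

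**Step 3: power at the planned effect, 20 mm on both, n = 27.** Power for one outcome is 0.9563 at level 0.025 and 0.9793 at level 0.05. With independent outcomes:
- Both, equal split: 0.9563² = 0.915.
- Both, Holm: 0.9793² − (0.9793 − 0.9563)² = 0.958.
- One given outcome, Holm: 0.9563 + (0.9793 − 0.9563) × 0.9563 = 0.978, against 0.956.

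**Step 4: one outcome weaker, 12 mm (d = 12/25 = 0.48, an assumption).** Noncentrality is 0.48 × √27 = 2.494. Power is 0.5525 at level 0.025 and 0.6705 at 0.05. With the other outcome at 20 mm and independent, Holm gives 0.5525 + (0.6705 − 0.5525) × 0.9563 = 0.665.

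**Step 5: correlated outcomes, by simulation.**

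| True effects | Correlation | At least one (both procedures) | Both: split → Holm | Second outcome: split → Holm |
|---|---|---|---|---|
| 20 and 20 mm | 0 | 99.8% | 91.5% → 95.9% | 95.6% → 97.8% |
| 20 and 20 mm | 0.5 | 99.1% | 92.4% → 96.1% | 95.7% → 97.6% |
| 20 and 20 mm | 0.8 | 97.9% | 93.3% → 96.3% | 95.6% → 97.1% |
| 20 and 12 mm | 0 | 98.1% | 52.8% → 65.4% | 55.3% → 66.6% |
| 20 and 12 mm | 0.5 | 96.4% | 54.5% → 66.3% | 55.3% → 66.6% |
| 20 and 12 mm | 0.8 | 95.7% | 55.2% → 67.0% | 55.3% → 67.0% |

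The chance of at least one success is the same under both procedures in every row, because Holm's first step also uses 0.025. For the same reason the sample size stays at 27.

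**The case against.** The strongest answer is that nothing here is wrong. The equal split controls the 5%, meets its 95% power, and serves the stated success rule of an effect on either outcome, which gains nothing from Holm. At the planned effect the gain is small. The larger gains need an effect below 20 mm, which the article does not assume. All of that stands, and it is why this is only an improvement.

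A reader might go further than the text and infer that the plan tests each outcome at 0.025 whatever the other shows, or that a second outcome with p between 0.025 and 0.05 would be declared negative. The article does not say so. The level appears only as a sample-size input, and Statistical methods gives none. Planning at 0.025 is also what someone intending Holm would do, so an analysis plan that is not shown could already specify it. Nor is the silence of Statistical methods a fault in itself, since an article commonly leaves such detail to the analysis plan.

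There is also a legitimate reason to prefer the split: its 97.5% confidence intervals agree with its tests, which has value in a proof-of-concept trial that aims to measure the size of the relief. What remains against the objection is that the split is the one rule a reader can take from the article, and a procedure that never rejects less is available without extra patients.

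**Conclusion.** The point holds as an optional, low-cost improvement. The one multiplicity rule stated, 0.025 per primary outcome, amounts to Bonferroni when read as written. It is valid and delivers the planned power. Holm is uniformly more powerful at the same two-sided 5% family-wise error, under any correlation.

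At the planned 20 mm on both outcomes the gain is about 2 points for a given outcome and 3 to 4 points for claiming both. It is 11 to 12 points for an outcome whose effect is only 12 mm. The chance of at least one success and the sample size do not change.

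The figures rest on 27 completers, an SD of within-patient differences of 25 mm for both outcomes, normal data, and a correlation between 0 and 0.8. The 12 mm effect and the correlation range are assumptions of this check and do not come from the article.

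**What to change.** Keep 0.025 and 27 in Sample size. In Statistical methods (or the analysis plan), before unblinding, add a sentence of this kind: the two primary outcomes are tested by Holm's procedure at a two-sided family-wise level of 5%, the smaller p-value against 0.025 and, if it is significant, the larger against 0.05. If the analysis plan already says this, it is enough to state it in the protocol as well.

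Report 97.5% confidence intervals for both outcomes, and say in advance that the interval for the second outcome may include zero although Holm rejects its null hypothesis.

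The cost is one sentence and that possible mismatch. No patients, visits or data are added. The timing matters, because a step-down rule chosen after the p-values are known would not be credible.

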### Recruitment and informed consent

The thirty-two patients, females and males, with post-traumatic peripheral neuropathic pain will be recruited from the Quebec Pain Registry (more information available at www.quebecpainregistry.com) and the Alan Edwards Pain Management Unit at the Montreal General Hospital.

Informed consent is obtained by research study staff that have obtained Good Clinical Practice (GCP) clinical research training certification by the Research Institute of the McGill University Health Centre. Also, the research study staff will receive training on general standard operating procedures for clinical trials and specific tasks for conducting the study.

### Randomization and blinding

Randomization for treatment order (placebo–active drug/active drug–placebo) is performed by a coin flip done by a research coordinator assigned for this task who is not involved in patient interaction and outcome assessment. The same coordinator also ensures blinding by assigning a three-digit number code, from a computer-generated random list, to the Topi-Pumps used in each treatment block. The list of number codes and the identity of their corresponding treatment is only shared with the compounding pharmacy. The blinding applies to the patient, the study coordinator performing patient assessments, and the dispensing pharmacy.

### Implementation

The sequence of treatment for each patient will be determined based on the randomized treatment order assigned by the research coordinator described above. The enrolment and evaluation of eligible patients will be performed by two other research coordinators with the assistance of research nurses at the pain clinic. The two research coordinators and research nurses will be strictly blinded to the treatment allocations of the patients.

### Data collection, management, and confidentiality

Data will initially be collected on paper-based source documents filled out at every visit. Data will then be transferred promptly into a spreadsheet stored in a password protected drive. Data entry and management will be completed by one of the study coordinators and the sponsor will not have access to the data. All source documents and data sheets used in the clinical trial will not have patient identifying information; instead, patients will be assigned a study code number with the key securely stored to ensure confidentiality. All information pertaining to the study will be retained by the principal investigator for 25 years after completion as per guidelines of Health Canada.

### Auditing

The MUHC-REB will perform an annual review of the study activities and progress before issuing a renewal of authorization to resume the study. The review will require a detailed report of the number of recruited and enrolled participants; a tally of participants that completed, dropped out, or withdrew from the study with explanations; and a description of the nature and frequency of adverse events recorded during the study. Regular inspections and audits are expected to be performed by delegates from the MUHC-REB and Health Canada. The study coordinators will facilitate the process by granting access to all paper and electronic study records and data. The coordinators will also accompany the auditor on any tours and inspections of the study area.

### Statistical methods

Statistical analysis will be performed using an unpaired *t-*test to evaluate between-group differences in the 2-sequence groups, as is recommended for analyses in cross-over designs [31]. The summarized VAS pain scores during the second week of treatment will be compared between treatment groups adjusting for period and order. We will also use unpaired *t-*tests to assess carry-over effects by comparing baseline and washout period measures. DMA pain scores at the end of each treatment period will also be compared between treatment periods. Secondary analyses of pain relief and the area of punctate hyperalgesia will also be conducted using unpaired *t*-tests.

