## Methods

### Trial design

This trial uses a randomized, double-blind, placebo-controlled cross-over study design. In this counterbalanced cross-over study, enrolled patients will be treated with active drug and placebo for periods of 2 weeks each, with an intervening 1-week washout period (Fig. 1).

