### Study process

A summary of the study process is outlined in Table 1. The first screening visit will entail obtaining informed consent; reviewing patients’ medical history, including the patients’ current medications; performing sensory tests for mechanical sensitivity; collecting blood samples for liver and kidney function; and obtaining urine samples from pre-menopausal women for a pregnancy test. Patients will be provided with a pain diary to record their daily pain intensity for the 7 days that follow the screening visit. Patients with normal laboratory test results of liver and kidney function will be contacted over the phone. After the assessment of pain diaries for pain intensity, patients that meet the eligibility requirements of the study (see below) will be provided with study drugs according to the treatment regimen assigned for the first 2 weeks of the trial. Regular medications used before enrolment into the study will be continued.

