**Table 1 Tab1:**
[figure not shown]
Study process

Throughout each treatment period and during the washout, patients will be asked to record their average pain scores in a pain diary, once daily in the evening. At the beginning and end of each treatment block, sensory testing will be performed to determine the degree of dynamic mechanical allodynia and area of punctate hyperalgesia. At the end of each treatment block, patients will be asked to score the degree of their overall pain relief. Adverse events will also be captured at the end of each treatment block and after the washout week.

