## Discussion

The peripheral neuropathic pain patient population is composed of a sizable number of patients that can benefit from avoiding the systemic anticonvulsants and antidepressants that are first-line treatments of the condition [3–5]. Given their typically older age and comorbid conditions, these patients are at greater risk of developing adverse events from these recommended systemic treatments [4, 5]. This clinical study is a required step in developing a locally-administered, potentially effective and tolerable analgesic alternative for the treatment of peripheral neuropathic pain.

As a phase II clinical trial, this study is a proof-of-concept step to evaluate the potential efficacy and safety of the topical combination of clonidine and pentoxifylline in peripheral neuropathic pain [35]. To optimize the detection of hypothesized analgesic effects, the selection of the study population is restricted to a specific subgroup of neuropathic pain patients with an uncomplicated medical profile.

The cross-over design of the study was another step taken to increase the efficiency of the initial screening of the formulation’s analgesic effects. The design allows the use of a relatively small number of patients by minimizing between-subject data variability thereby reserving resources and time [35, 36]. We believe the 2-week duration of treatment is long enough to reveal the alleviation of neuropathic pain symptoms achieved. At the same time, the treatment is set to be brief enough to avoid long-term effects that can potentially change the underlying pathology preventing effective washout. The 1-week-long washout period is based on evidence obtained from the pharmacokinetics of constituent drugs and the length of analgesic effects measured from neuropathic rodent models and healthy volunteers treated with the formulation [25, 28, 33, 37]. It is expected that this time frame is sufficient in duration and carry-over effects are unlikely to occur.

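### As worded, the carry-over check compares baseline with washout in the same patients by an unpaired t-test, so it is mis-sized and does not isolate carry-over

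*Protocol article*

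**What the plan says.** In Statistical methods, the treatment effect is tested with an unpaired t-test "to evaluate between-group differences in the 2-sequence groups, as is recommended for analyses in cross-over designs". Two sentences later, unpaired t-tests are also assigned to carry-over, and will "assess carry-over effects by comparing baseline and washout period measures". That sentence mentions neither the sequence groups nor a change score.

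The source of the two measures is clear. Under Study process, patients "record their daily pain intensity for the 7 days that follow the screening visit", which gives the baseline diary. The same section continues: "Throughout each treatment period and during the washout, patients will be asked to record their average pain scores in a pain diary". Sensory testing is done at the start and end of each treatment block. Under Trial design, "enrolled patients will be treated with active drug and placebo for periods of 2 weeks each, with an intervening 1-week washout period", so the washout follows active drug in one sequence and placebo in the other.

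The Discussion says of the one-week washout: "It is expected that this time frame is sufficient in duration and carry-over effects are unlikely to occur".

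**The concern.** Three things go wrong if the carry-over sentence is carried out as worded.

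1. **Error term.** Each patient supplies a baseline value and a washout value. An unpaired test treats them as independent and, when they are positively correlated, overstates the standard error.
2. **Contrast.** The carry-over that biases an active/placebo cross-over is the difference between the washout after active drug and the washout after placebo. Comparing all washout values with all baseline values ignores sequence and halves any signal that exists only in active-first patients.
3. **Common change.** Anything that moves both sequences alike enters the contrast. Regression to the mean is one plausible source, because patients qualify on a minimum pain level in the week before the study. A lasting placebo response is another.

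At stake is the interpretation of the one named carry-over check in patients. A non-significant result could seem to confirm the Discussion's expectation when the test had little chance of rejecting. A significant one could cast doubt on the second period because of a harmless drift.

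**Working it through.** **The plan's own figure.** The article gives no figure for the carry-over test, only a required sample size of 27 for the treatment comparison. With d = 20/25 = 0.8, two-sided alpha 0.025 and a paired t-test, exact power at n = 27 is 95.6%, so 27 reproduces. It requires 25 mm to be the SD of the within-patient difference, or equivalently a per-period SD of 25 mm with correlation 0.5, since 25 × √(2 × (1 − 0.5)) = 25.

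**Inputs for the carry-over check**
- From Sample size: N = 32 and SD 25 mm, taken here as the SD of a single measure; and, for scale, a design effect "of 20 mm or more on the 100 mm VAS".
- Assumed, because not stated: 16 patients per sequence, nominal two-sided 5%, correlation ρ between baseline and washout of 0.5 or 0.7, and the sizes of drift and carry-over.

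**The test as worded**
- Standard error it uses: 25 × √(2/32) = 6.25 mm. With a critical t of about 2.00, it needs an observed difference of about 12.5 mm.
- True standard error of that difference: 25 × √(2(1 − ρ)/32) = 4.42 mm (ρ = 0.5) or 3.42 mm (ρ = 0.7).
- Large-sample size: 2 × [1 − Φ(1.96/√(1 − ρ))] = 0.56% or 0.03%. Simulation gives about 0.7% and under 0.1%. At ρ = 0 the size is correct.
- A carry-over of c mm in active-first patients only shifts the pooled difference by c/2. So a real 20 mm carry-over and a common 10 mm fall both give an expected difference of 10 mm, and the test can hardly tell them apart.

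**The between-sequence test** takes each patient's baseline-to-washout change and compares active-first with placebo-first patients.
- SD of change: 25 × √(2(1 − ρ)) = 25.0 or 19.4 mm.
- Standard error: SD × √(2/16) = 8.84 or 6.85 mm.
- 95% CI half-width at t(30 df) = 2.042: about 18 or 14 mm.
- A common change cancels.

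Simulated rejection rates (at least 20,000 trials per cell), each cell giving ρ = 0.5 / ρ = 0.7:

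| Scenario | As worded | Between sequences |
|---|---|---|
| No carry-over, no drift | 0.7% / <0.1% | 5% / 5% |
| Common fall 5 mm | 5% / 2% | 5% / 5% |
| Common fall 10 mm | 30% / 26% | 5% / 5% |
| Carry-over 10 mm | 5% / 2% | 19% / 29% |
| Carry-over 20 mm | 26% / 21% | 59% / 81% |

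Moving to a paired test of baseline against washout restores the size to about 5% but not the meaning: it flags a common 10 mm fall in 59% of trials at ρ = 0.5.

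**How large might the drift be?** Suppose the entry rule acted like a cut of the baseline mean at 40 mm in a source population with SD 25 mm. The expected fall is (1 − ρ) × 25 × φ(k)/Φ(k), with k = (source mean − 40)/25.
- Source mean 40: φ/Φ = 0.798, so the fall is 10.0 mm (ρ = 0.5) or 6.0 mm (ρ = 0.7).
- Source mean 60: φ/Φ = 0.368, so the fall is 4.6 or 2.8 mm.

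Simulated with that truncation, the test as worded rejects in 7–53% of trials at ρ = 0.5 and 1–18% at ρ = 0.7. The rule of three days in the week may select less sharply than this.

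**The case against.** The strongest defence is that a between-sequence test was meant. The section opens with an unpaired t-test between the two sequence groups, and the carry-over sentence adds that unpaired t-tests will also be used there. On that reading, baseline and washout are only the ingredients and the sequences are the groups, which makes the test correctly sized and immune to a common drift. This reading is possible. It does not remove the point, because the sentence names baseline and washout as the things compared and mentions neither sequence nor change. Nor is it simply a detail left to a fuller document: the article states a test and a contrast, and the two do not fit together.

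Other parts of the defence stand:
- No decision rule hangs on the check. The article proposes no switch to first-period data.
- The primary comparison adjusts for period and order. In this design an order effect is aliased with differential carry-over, so carry-over could also show there, though not as a clean test.
- The correlation and the drift sizes are not in the document. A reader might infer that the test will routinely mistake a time trend for carry-over. The document does not support that: eligibility requires stable pain, and a 5 mm fall is flagged in only 2–5% of trials.
- The between-sequence test also misses most moderate carry-over at this sample size.

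**Conclusion.** The point holds for the sentence as worded. The error term is wrong, in the conservative direction. The contrast does not isolate the between-sequence difference, and a common fall of 10 mm is flagged about as often (26–30%) as a real 20 mm carry-over (21–26%). These figures assume a single-measure SD of 25 mm, a correlation of 0.5 to 0.7, equal sequences and a nominal 5% level. At correlations near zero the size problem disappears, but the contrast problem does not.

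A reader might go further and infer that the trial's efficacy result is compromised. The article does not support that. The check is supportive, nothing is made conditional on it, and the primary treatment contrast is not itself invalidated. Severity is moderate.

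**What to change.** Replace the carry-over sentence with one that names the groups and the quantity. For each patient, compute washout-week mean VAS minus screening-week mean VAS and, for brush-evoked allodynia, the score at the start of the second block minus that at the start of the first. Compare these changes between active-first and placebo-first patients with an unpaired t-test, and report the estimated difference with its 95% CI.

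Add that a non-significant result will not be read as showing that carry-over is absent. If a between-sequence comparison was always intended, the same sentence settles it. Merely changing to a paired baseline-washout test would not be enough.

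The cost is one or two sentences. The diary data and block-start sensory tests are already collected, so no visit, measurement or patient is added.

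### The comparison stated for dynamic mechanical allodynia (DMA), a primary outcome, is between treatment periods with no period adjustment, at odds with the rest of the section; it should use the period-adjusted sequence-group analysis

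*Protocol article*

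**What the plan says.** The Outcomes section of the protocol article lists DMA as the second of two primary outcomes, scored on a 100 mm VAS after a single brush stroke. The Sample size section allows success on either one ("spontaneous pain or intensity of DMA"), with alpha 0.025 corrected for multiple testing. A positive DMA result could therefore carry the efficacy claim alone.

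Three sentences in Statistical methods bear on how DMA is analysed:

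- The opening rule is an unpaired t-test "to evaluate between-group differences in the 2-sequence groups, as is recommended for analyses in cross-over designs". It is tied to no outcome.
- For spontaneous pain: "The summarized VAS pain scores during the second week of treatment will be compared between treatment groups adjusting for period and order".
- For DMA: "DMA pain scores at the end of each treatment period will also be compared between treatment periods". It names no test, no treatment contrast and no adjustment.

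Under Randomization and blinding, treatment order is set by a coin flip. No blocking is described, so equal sequence groups are not guaranteed.

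**The concern.** Between the two primary outcomes the stated contrast changes from treatments to periods, and the adjustment drops out. In a two-period cross-over those are different quantities. A comparison of period 1 with period 2 pools patients on active drug and on placebo within each period, so the drug effect largely cancels and a time trend remains. A comparison of the active with the placebo period does contain the drug effect, but any period effect enters it whenever the two sequences differ in size.

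With the text as it stands, three analyses of a primary outcome could each be defended: period against period, active against placebo unadjusted, and the sequence-group test. That choice should not be open once data are unblinded.

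**Working it through.** **Inputs.** From Sample size: a reduction "of 20 mm or more on the 100 mm VAS"; "standard deviation assumed: 25" (mm), giving d = 20/25 = 0.8; alpha 0.025; power 95%; 27 patients required and 32 recruited. The article does not say whether 25 mm is the SD of a score or of the within-patient difference, nor whether alpha is one- or two-sided. It gives no period effect, so 0, 5 and 10 mm are assumptions.

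**1. The plan's own figure.** Paired t-test on the within-patient difference, two-sided alpha 0.025, noncentrality d√n:
- n = 27: 0.8 × √27 = 4.16, power 95.6%
- n = 26: power 94.8%

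So 27 is reproduced if 25 mm is the SD of the within-patient difference and alpha is two-sided. Both are assumed below.

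**2. What each reading estimates.** Let τ be the drug effect (a 20 mm reduction is −20), π the period effect (period 2 minus period 1), n1 the number receiving active first, n2 the number receiving placebo first, and N = n1 + n2. The within-patient difference, period 2 minus period 1, has mean π − τ for active first and π + τ for placebo first.

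- (a) Period 2 against period 1: π − τ(n1 − n2)/N. At n1 = n2 this is π, and the drug effect is absent.
- (b) Active against placebo, unadjusted: τ − π(n1 − n2)/N.
- (c) Half the difference between sequence-group means: [(π + τ) − (π − τ)]/2 = τ, at any split.

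**3. Reading (a).** Simulated rejection rates:
- τ = −20, π = 0, 16:16: rejects in 0.4% of trials.
- τ = 0, 16:16: rejects in about 12.5% when π = −5 and 47% when π = −10.

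**4. Reading (b) in a given trial.** The shift is |π| × |n1 − n2|/N:
- 16:16: 0 mm
- 20:12, 5 mm period effect: 5 × 8/32 = 1.25 mm
- 20:12, 10 mm period effect: 10 × 8/32 = 2.5 mm
- 18:9, 10 mm period effect: 10 × 9/27 = 3.3 mm

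The sign depends on which sequence is larger. With τ = −20 and π = −10, the estimated reduction is 16.7 mm at 18:9 and 23.3 mm at 9:18. With no drug effect, type I error at 18:9 is about 4.3% against the nominal 2.5%.

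Simulated power with τ = −20 and π = −10:

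| Split | (b) unadjusted | (c) sequence-group |
|---|---|---|
| 14:13 | 92.6% | 95.5% |
| 18:9 | 81.3% | 93.0% |
| 20:12 | 91.7% | 97.5% |

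**5. Reading (b) averaged over the coin flip.** With 27 patients and π = −10, the mean estimate is −20.0 mm, type I error is 2.5% and power is 92.3%. With π = −5, power is 94.9%. With no period effect it is 95.6%.

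**6. How uneven a coin flip gets.** With 32 patients, exactly 16:16 has probability 14%, and a difference of 6 or more has probability 38%. With 27 patients, a split of 18:9 or worse, in either direction, has probability 12%.

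**7. Cost of the period-adjusted test.** At 14:13 the standard error is (25/2) × √(1/14 + 1/13) = 4.81 mm. The noncentrality is 20/4.81 = 4.15 on 25 degrees of freedom, and power is 95.5%, against 95.6% for the unadjusted paired test when there is no period effect.

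**The case against.** The best defence is that the section already contains the right analysis. Its opening rule compares the two sequence groups and is restricted to no outcome. Applied to within-patient period differences, this is the standard cross-over test and removes an additive period effect. Nothing withdraws it for DMA. This stands, and it means the fault may be one of wording only. It does not settle the matter: the opening rule does not say that the t-test is applied to period differences, and the DMA sentence then names a different contrast.

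A reader might infer the stronger claim, that the planned DMA analysis tests period 1 against period 2 and so cannot detect the drug. The article does not support that. Sample size uses the term treatment period for the time on active drug, and the trial is powered for a 20 mm reduction in either primary outcome on active treatment. The active-against-placebo reading is therefore much the likelier, and the 0.4% rejection rate describes an analysis that was probably never intended.

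A reader might also infer that the active-placebo comparison is systematically confounded with time. It is not: a coin flip gives the period effect a random sign for each patient, so the estimate is unbiased on average (step 5). The 18:9 split with a 10 mm period effect is an unfavourable case built on an assumption.

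Finally, an article condenses its protocol and need not repeat an adjustment for every outcome. That would excuse silence. Here a contrast is stated for a primary outcome, and it differs from the one stated for the other.

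**Conclusion.** The point holds as an inconsistency in the stated analysis of a primary outcome. It does not show that the trial is unable to estimate the drug effect on DMA.

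On the likely reading, the consequence is modest: nothing if there is no period effect; a shift of about 1 to 3 mm against the 20 mm target in the unequal splits worked above, if the period effect is 5 to 10 mm; and a loss of power of about 3 percentage points at 14:13 and 12 at 18:9 for a 10 mm period effect. If the opening rule was meant to govern DMA, there is no numerical consequence and only the contradiction needs removing.

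These sizes rest on assumed period effects, on 25 mm being the SD of the within-patient difference, and on two-sided alpha. The case for changing the sentence does not depend on them, because the period-adjusted test recovers the drug effect at any split and costs almost nothing when there is no period effect.

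**What to change.** Replace the DMA sentence in Statistical methods with: *DMA at the end of each treatment period will be compared between active and placebo using the same sequence-group t-test on within-patient period differences (period-adjusted) as for spontaneous pain, at alpha 0.025.* State there whether alpha is two-sided, which is what the sample size of 27 implies. Carry the same wording into the full protocol and any SAP before unblinding.

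The cost is one sentence. No new data, visits or patients are needed, and the sample size stays as it is.
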